**Secondary outcome measures:**		
Hand pain #	Numeric rating scale (NRS): 0-10	0, 3, 6
Hand stiffness #	Numeric rating scale (NRS): 0-10	0, 3, 6
Patient Global Assessment of disease activity #	NRS: 0-10	0, 3, 6
Patient Global Assessment of disease activity affecting activities of daily living #	NRS: 0-10	0, 3, 6
Patient Global Assessment of change in disease activity over past three months #	7-point scale	3, 6
Patient Global assessment of change in management of activities of daily living #	5 point scale	3, 6
Grip strength (JAMAR dynamometer)	Kilogramme (mean of three repetitions)	0, 3, 6
Hand dexterity (Moberg Pick-up Test [38])	Seconds (right hand, left hand)	0, 3, 6
Thumb web space (Grip Size instrument)	Cylinder size: 1–12 cm	0, 3, 6
Health-related quality of life (15D [39])	0-1 scale	0, 3, 6

*0 = baseline, 3 = 3 months, 6 = 6 months.

# Items included in the telephone interview when attendance is impossible.

**Table 4 T4:** Tertiary outcome measures

**Tertiary outcome measures**	**Measurement scale**	**Time***
Hand pain in which hand	Left/Right/Both	0, 3, 6
Which hand is most painful	Left/Right	0, 3, 6
Hand injury, surgery or injections over past three months	Single question	3, 6
Fatigue	Numeric rating scale (NRS): 0-10	0, 3, 6
Mental distress (General Health Questionnaire, GHQ-20 [40])	Bi-modal fashion (0-0-1-1)	0 months
Self-reported work ability [41]	5-point scale	0, 3, 6
Physical activity (International Physical Activity Questionnaire-Short Form, IPAQ [42])	Mean minutes/week, MET-minutes/week	0, 3, 6
• Vigorous-intensity activity		
• Moderate-intensity activity		
• Walking		
• Sitting		
Exercise self-efficacy [43]	7-point scale	0, 3, 6
Exercise diary (intervention group only)	dd.mm.yy	0-3
• Date	Minutes	
• Exercise duration	NRS: 0–10	
• Pain level post-exercise	Text	
• Comments	Kilogrammes	
• Grip strength at group sessions (weeks 2, 3 and 8)		
Adverse events (intervention group only, obtained from the exercise diary + telephone follow-up log)	Type, duration	0-3

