### Blinding

The outcome assessors are blind to group allocation, and are not involved in providing the interventions. The written participant information tells participants that they have an equal chance of being randomised to the intervention versus the control group, but does not provide any details of the actual exercise programme. Allocation is revealed to the three occupational therapists delivering the intervention (group exercises and telephone follow-up), but participants are requested not to disclose details about their group allocation with the outcome assessor. The success of outcome assessor blinding will be evaluated during one group follow-up assessment for the outcome assessors in Ullensaker and one at Diakonhjemmet Hospital by asking the assessors to guess the participants’ group allocation. The statistician who will perform the main statistical analyses will be blinded to group allocation during the analyses.

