### Intervention

Both the control and intervention groups receive “usual care”, which for most people in Norway with hand OA is limited to general practitioner visits (or infrequently, a referral to a consultation with occupational therapists in secondary care). During this study, the control group receives no particular attention, referral or treatment from the project group, and we expect that none, or only a few, will consult a health care professional for their hand OA. Only the intervention group receives the exercise intervention, including the telephone follow-up.

The exercise programme for people with hand OA was developed in 2010 based on the results from a systematic review of the design and effects of splints and exercise programmes, as well as from the American College of Sports Medicine (ACSM) recommendations for developing muscular strength and flexibility in older frail adults [12,27]. The development of the exercise programme followed the new Medical Research Council guidance [28] for developing and evaluating complex interventions, including pilot testing (manuscript under review). Exercises 1–3 aim to increase the muscular strength and stability of the shoulder girdle/upper arm muscles, as this may influence hand activity performance. Exercises 4–5 intend to maintain or increase the flexibility of the MCP, PIP and DIP joints, while exercise 6 aims to strengthen the mm. extensors and abductors pollicis. The purpose is to maintain the thumb web space, increase thumb stability and counteract the strong pull from the adductor pollicis muscle combined with increasing the weakness of the opposing thenar intrinsic musculature, which can be seen in individuals with CMC1 OA, thereby leading to thumb adduction deformity. Exercise 7 intends to increase grip strength. Pipe insulation tubes were chosen instead of balls or other round objects since the tubes allow for squeezing without involving the thumb adductor muscles, which may contribute to a thumb adduction deformity. For the same reason, there is no exercise included to increase the maximum opposition of the thumb (touch the base of the little finger with the thumb tip) or to strengthen the pinch or key grip, as such exercises may accelerate an evolving CMC1-deformity.

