8.		**Finger stretch:** Lay the right hand on a flat surface. Use the left hand to apply firm pressure for 30 seconds stretching the 2nd to 5th PIP and DIP joints. Repeat 2 times for each hand.
		If the finger joints are painful: stretch one finger at a time; place the 2nd to 4th finger tips (opposite hand) between the finger joints of the 2nd finger; press for 30 seconds.

*The person on the images has consented for the images to be published.

The intervention group attends one group session per week and does two home sessions per week in weeks 1–3. During weeks 4–7 and 9–12 they do three sessions per week on their own. There is a “booster” group session in week 8 to ensure adherence and to individually adjust the exercises. The group sessions last approximately 45 minutes, and are conducted in the afternoon in the locations of the Ullensaker Primary Health Care and at Diakonhjemmet Hospital. SMS reminders are sent one day in advance, and the intervention group additionally receives a weekly telephone call in the weeks without group sessions (weeks 4–7 and 9–12) for individualised advice that addresses the exercises and encourages programme adherence.

The intervention group keeps the exercise equipment after the intervention period and decides themselves if they want to continue performing the exercise programme. Moreover, no advice is given to the control group at this time, but after the 6-month follow-up, the control group is provided with exercise equipment and instructions in the exercise programme. The Ullensaker cohort will most likely be naïve to hand exercises, while some of the Oslo Hand OA cohort may have received instructions at Diakonhjemmet Hospital Outpatient Clinic in 2007/2008. The Oslo Hand OA cohort control group participants will be asked whether they have received instructions in hand exercises before. At the two follow-ups all participants in the control group will be asked whether they have performed hand exercises in the past 3 months.

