### Adverse effects or events

Adverse events related to exercises for people with hand OA are not consistently studied, but the risk is considered to be low if the suitability of the exercise for the individual is appropriately assessed by a trained health professional [8,51]. Should they occur, adverse events related to the exercise intervention are documented by the type and duration, and information on this is collected and registered during telephone counseling and from the exercise diary.

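### Adverse events are recorded only in the exercise arm and only to month 3, so their rates cannot be compared between arms; other measures allow only a partial comparison

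*Protocol article*

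**What the plan says.** Table 4 (tertiary outcomes) restricts the item by arm and source: "Adverse events (intervention group only, obtained from the exercise diary + telephone follow-up log". The same row gives the content and window: "telephone follow-up log) Type, duration 0-3".

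The section Adverse effects or events states that "adverse events related to the exercise intervention are documented by the type and duration" and that "information on this is collected and registered during telephone counseling and from the exercise diary".

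The control arm has neither source. The diary row in Table 4 is for the intervention group alone, the Intervention section gives telephone follow-up only to that group, and it says that "the control group receives no particular attention, referral or treatment from the project group".

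Exposure may outlast the recording window. On the period after week 12, the Intervention section says: "The intervention group keeps the exercise equipment after the intervention period and decides themselves if they want to continue performing the exercise programme". Under Data analysis, self-reported exercise frequency and duration are to be described at both 3 and 6 months.

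The Outcome measures section, citing Tables 3 and 4, says that every outcome is collected at baseline, 3 months and 6 months. The adverse event row does not fit that sentence.

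**The concern.** The protocol fixes a one-arm rule in plain terms, so this is not a detail that the article has left to a fuller document. The Background section lists pain and soft tissue swelling among the features of hand OA itself. Such events will occur in untreated people, and a count among exercisers has no meaning without a count, taken in the same way, among controls.

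The protocol gives its own reasons to want that comparison. It says that harms of hand exercise have not been studied consistently. It leaves out certain thumb exercises for fear of worsening a deformity. It asks for moderate to vigorous effort with progression, and it offers the programme to controls after month 6. A randomised trial could supply a comparative estimate of harm. As written, this one cannot do so for adverse events.

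**Working it through.** **Plan's own figure.** The documents state no adverse event rate and no precision target, so there is none to reproduce. The only input taken from the plan is the group size. For FIHOA (difference 3, SD 6.2, two-sided 5%, power 80%), n = 2 × (1.96 + 0.84)² × 6.2² / 3² ≈ 67.1, rounded up to 68, as stated. Then 68 × 1.10 = 74.8, giving the stated 75. Dividing by 0.90 gives 76; that difference is not a finding.

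**What is recorded, by arm and period.**

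| Information | Exercise, months 0–3 | Control, months 0–3 | Exercise, months 3–6 | Control, months 3–6 |
|---|---|---|---|---|
| Adverse events (diary, telephone log) | yes | no | no | no |
| Hand pain, stiffness, global assessment, grip strength | at visit | at visit | at visit | at visit |
| Change in disease activity, past three months (7-point) | yes | yes | yes | yes |
| Injury, surgery, injections, past three months | yes | yes | yes | yes |
| Hand OA medication and health-care visits, past three months | yes | yes | yes | yes |

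The first row comes from Table 4 and the section Adverse effects or events. The others come from Tables 3 and 4 and the sections on secondary and tertiary outcomes. Only the first row lacks a randomised comparison. The other rows either measure status at a visit or ask about specific consequences. A flare that settles between visits, or an event that leads to no injury, injection, medication or consultation, can escape all of them.

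**What the plan can report now.** A one-arm proportion. For example, 15/75 = 20%, exact 95% CI 11.6% to 30.8%; with 0/75 the upper limit is 4.8%. No risk difference can be formed.

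**What identical recording in both arms would give.** The background risk p is an assumption, shown over 5–30%.

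- Half-width of the 95% CI for the risk difference, with equal risks and n = 75: 1.96 × √(2p(1 − p)/75). At p = 0.05 this is 1.96 × √(0.095/75) = 0.070; at p = 0.30 it is 1.96 × √(0.42/75) = 0.147.
- Power for an excess d, with p₁ = p + d and p̄ the mean of the two risks: Φ{[d − 1.96√(2p̄(1 − p̄)/75)] / √([p(1 − p) + p₁(1 − p₁)]/75)}.

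| Assumed background risk | Half-width (percentage points) | Power, 10-point excess | Power, 20-point excess |
|---|---|---|---|
| 5% | 7.0 | 0.53 | 0.94 |
| 10% | 9.6 | 0.40 | 0.87 |
| 20% | 12.8 | 0.29 | 0.77 |
| 30% | 14.7 | 0.25 | 0.71 |

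With 68 per arm the half-widths are 7.3 to 15.4 points. The added item would inform on a large excess of events, not a small one.

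**The case against.** A reader might infer that the trial cannot tell harm from the natural course of hand OA. The documents do not support that. A sustained worsening caused by exercise would show as a randomised difference in pain, stiffness, global change or grip strength, and its consequences could show in injections, medication or health-care use. For the same reason, 0 of 75 controls applies only to items labelled as adverse events, and months 3–6 are not blank for harm in general.

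A reader might also infer that staff decide on relatedness before recording anything, which would bias ascertainment. The wording in Adverse effects or events limits what is documented, but no adjudication step is described. The Table 4 row carries no such limit, and the diary takes post-exercise pain and free comments without a filter. Nor do the documents say that flares will be attributed to exercise or dismissed; no causal statement or between-arm test is planned for this tertiary item.

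The lack of blinding is not a separate fault that the fix would cure. It is true that "Allocation is revealed to the three occupational therapists delivering the intervention (group exercises and telephone follow-up", whereas "The outcome assessors are blind to group allocation, and are not involved in providing the interventions". But participants know their arm and there is no sham, so any self-reported item is unblinded too.

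Finally, the protocol gives a rationale for light recording: the risk is thought low when a trained professional assesses suitability. Controls are left alone by design, and the primary outcome is untouched. All of that stands, and it narrows the point. It does not supply a control rate for flares or other events, and a question on a questionnaire that controls already complete would add little contact.

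**Conclusion.** The point holds in a limited form. Followed exactly, the plan records adverse events in one arm, for 0–3 months, from sources that controls do not have, and it confines them to events related to the exercise. Adverse event rates therefore cannot be compared between arms, and no adverse event recording is stated for months 3–6 although exercise may continue. The measures collected in both arms allow a partial comparison; what they leave uncovered is transient flares and other event types. The factual part rests on the text alone. The precision figures rest on 75 per arm and an assumed background risk of 5–30%, and serve as illustration. The change is worth making, but it does not affect the primary analysis.

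**What to change.** - Add one identical item to the 3- and 6-month questionnaires in both arms: any adverse event in the past three months, whatever its cause (yes/no, type, duration).
- Report counts by arm at each visit with a risk difference and 95% CI.
- Keep diary and telephone events as a separate listing for the intervention arm, not pooled with the questionnaire item.
- Reconcile the adverse event row of Table 4 with the sentence in Outcome measures on time points.
- For participants without the item, state that adverse events are non-comparative and draw no causal safety conclusion from them.

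Cost: one item on two existing questionnaires and a minor amendment. Three-month recall is coarse, answers are unblinded, and precision is low. The article describes recruitment as under way, so participants already past a visit will lack the item; the intervals will then be wider than those shown for 75 per arm.

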**Direct and indirect costs**		
Self-reported sick leave over past three months	Number of days	0, 3, 6
Absence from non-paid work over past three months	Number of days	0, 3, 6
Self-reported health-care utilisation over past three months: number of visits to general practitioner, medical specialist, physiotherapist, manual therapist, chiropractor, occupational therapist, psychologist, social worker, nurse at general practice/outpatient clinic, “alternative therapy”, hospitalisation	Number of visits	0, 3, 6
Pharmacology use for hand OA over past three months	Self-reported	0, 3, 6
Medical or technical equipment purchased during the past three months	Self-reported	
Costs for attending group sessions (only intervention group): distance travelled, transportation method, transportation costs, work absence, need for accompaniment	Self-reported	0
**Participant characteristic variables**		
Age	Birth year	0
Gender	Female/Male	0
Marital status	Married or cohabiting/Separated or divorced/Widowed/Single	0
Education	Lower secondary school/Higher secondary school/University 1–4 years/University >4 years	0
Employment status	Working full time/working part time/not working/student/working full-time in the home/unemployed or seeking work/age retired/disability pension/sick leave	0
Height	Centimetres	0
Weight	Kilogrammes	0
Dominant hand	Left/Right	0
Year of OA diagnosis	Year	0
Fulfilment of ACR criteria for hand OA	Yes/no	0

*0 = baseline, 3 = 3 months, 6 = 6 months.

### Primary outcome measures

The primary outcome measure is self-reported hand activity performance, as measured by the the Functional Index for Hand OsteoArthritis (FIHOA) [36] and the Patient-Specific Function Scale (PSFS) [37].

The FIHOA consists of 10 items with a four-point Likert scale: “possible without difficulty” (0), “possible with slight difficulty” (1), “possible with important difficulty” (2) and “impossible” (3). In this study, it is used as a patient self-administered instrument, and a total score is calculated, with 0 indicating a good performance and 30 indicating a very poor hand activity performance. The instrument has previously been translated from French to Norwegian using a forward-backward translation that followed recommended procedures [44], and evidence for test-retest reliability, validity and responsiveness has been shown [36,45,46].

The PSFS is a patient-specific instrument commonly used in assessments and evaluations in musculoskeletal pain disorders. The instrument is interview-administered, and the patient is asked to name three to five important activities that they are unable to do or have difficulty doing as a result of their problem (in the present study: their hand OA). The patient then scores the difficulty on an 11-point numeric rating scale (NRS), in which 0 represents “Unable to perform activity” and 10 “Able to perform activity at pre-injury/disease level”. The scores for each activity are used independently and no total score is calculated. In a recent systematic review, the instrument’s measurement properties have been found to be acceptable for several musculoskeletal disorders [47], and it was found to be responsive in patients with musculoskeletal disorders receiving physiotherapy treatment in primary care [48].

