### Outcome measures

The outcome measures have been selected based on those recommended for clinical trials in patients with hand OA [34,35], and consist of a combination of patient self-reported outcomes and performance tests. All outcome measures are collected at baseline, 3 months (post-intervention, primary endpoint) and 6 months (Tables 3 and 4). If a participant is unable to attend the assessment on the given date (i.e. due to vacation, sickness, etc.), a new appointment is made. For extraordinary situations (i.e. long-term vacation), the questionnaire is sent by mail/e-mail or the most important outcome measures (marked in Table 3) are collected in a telephone interview.

**Table 3 T3:** Primary and secondary outcomes

**Primary outcome measures:**	**Measurement scale**	**Time***
Hand activity performance (The Functional Index for Hand OsteoArthritis, FIHOA [36]) #	0-30	0, 3, 6
Patient-generated disability (Patient-Specific Function Scale, PSFS [37]) #	0-10	0, 3, 6

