### Statistical analyses

#### Data analysis

Demographic and clinical characteristics as well as other baseline data are being collected and will be presented to assess the baseline comparability of the two groups. These variables will also be compared for those participants who withdraw from the study and those who remain. Parametric and non-parametric statistical analysis models will be used depending on the distribution of the variables.

The intention-to-treat principle (ITT) will be followed in the primary analyses of data, and will include all participants, also those who have missing data and those who are not fully compliant with the protocol. Descriptive statistics will be presented for each group as the mean change (standard deviation, 95% confidence intervals) in the outcomes from baseline to each time point. Differences in mean change from baseline to each time point will be compared between groups, using linear mixed models or generalised linear regression modeling, adjusting for baseline levels of the outcome measure. Model assumptions will be checked by standard diagnostic plots, and improvements in the intervention and control group based on the perceived ratings of change will be compared using logistic regression, and presented as odds ratios with 95% confidence intervals. Additionally, the number of “responders” in the two groups will be compared using the OMERACT-OARSI responder criteria [54]. A participant will be classified as a responder if one of the following is fulfilled:

1) High improvement:

•≥50% improvement + absolute change of ≥2 in self-reported hand pain (NRS, 0–10), OR

•≥50% improvement + absolute change of ≥6 in self-reported hand activity performance (FIHOA, 0–30);

OR

2) Improvement in at least 2 of the 3 following:

•≥20% improvement + absolute change ≥1 in self-reported hand pain

•≥20% improvement + absolute change ≥1 in Patient Global Assessment of disease activity (NRS, 0–10)

•≥20% improvement + absolute change ≥6 in self-reported hand activity performance (FIHOA)

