An exploratory sub-group analysis will be completed to examine the effectiveness of the exercise programme for those participants attending all group sessions and performing all home sessions. This analysis will only be completed if there are sufficient participants attending all four treatment sessions and performing all home sessions. Treatment concordance will also be evaluated descriptively by self-reported exercise frequency and duration at the 3- and 6-month follow-up.

Exact analyses utilising the binominal distribution will be used to assess the success of outcome assessor blinding (with 95% confidence intervals); no statistical adjustment will be made for multiple testing, and all tests will be two-sided and carried out at the 5% level of significance. Any changes to the study design or analysis plan will be documented with full justification.

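### PSFS is a primary outcome, but the scoring rule leaves it without a single participant-level endpoint or treatment contrast

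*Protocol article*

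**What the plan says.** The Primary outcome measures section of the protocol article opens with: "The primary outcome measure is self-reported hand activity performance, as measured by the the Functional Index for Hand OsteoArthritis (FIHOA) [36] and the Patient-Specific Function" (the quote stops within the name of the second instrument, the PSFS). Table 3 also lists the PSFS as primary, as one measure on a 0-10 scale at baseline, 3 and 6 months.

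For the PSFS, "the patient is asked to name three to five important activities that they are unable to do or have difficulty doing", and each activity is rated 0 to 10. The scoring rule is: "The scores for each activity are used independently and no total score is calculated". For the FIHOA, by contrast, "a total score is calculated, with 0 indicating a good performance and 30 indicating a very poor hand activity performance".

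The Data analysis section applies one approach to all outcomes: "Differences in mean change from baseline to each time point will be compared between groups", by a linear mixed model or a generalised linear regression with the outcome's baseline value as covariate. It adds that "no statistical adjustment will be made for multiple testing" and that "all tests will be two-sided and carried out at the 5% level of significance". The Sample size section uses the FIHOA only.

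**The concern.** The planned model needs one response and one baseline value per participant and time point, or a stated way of handling several. For the FIHOA that is the total. For the PSFS there are three to five numbers per person, and the article says they are kept apart. A mean is a total divided by the number of activities, so the natural reading excludes that as well.

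The omission is particular to the PSFS. Grip strength is averaged within each hand, and even the tertiary exercise self-efficacy questionnaire has a mean score.

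At stake is what the PSFS primary result is. Activity 1 is a different task for each participant, so a test on it has no common meaning across people. Activities 4 and 5 exist only for those who named that many, so tests on them cannot include all participants, as the intention-to-treat statement promises. With several analyses open and no adjustment allowed, the error rate of a PSFS claim depends on a choice that the text does not fix.

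**Working it through.** **The plan's own figure.** The inputs are in the Sample size section: difference 3, SD 6.2, two-sided 5%, power 80%.

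n per group = 2 × [6.2 × (1.960 + 0.842) / 3]² = 67.05, rounded up to 68, as stated. For 10% drop-out, 68 × 1.10 = 74.8 (75, as stated) and 68 / 0.90 = 75.6 (76). The figure reproduces to within one person per group. It concerns the FIHOA total only, so nothing below changes it.

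**Reading A: each activity tested separately.** The inputs are k = 3 to 5 activities (Primary outcome measures) and 5% per test without adjustment (Data analysis). For independent tests, P(at least one false positive) = 1 − 0.95^k:

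- k = 3: 1 − 0.857 = 14.3%
- k = 4: 1 − 0.815 = 18.5%
- k = 5: 1 − 0.774 = 22.6%

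The scores come from the same people, so the tests are probably correlated. The article gives no correlation. A simulation with 1,000,000 draws of equally correlated normal test statistics gives:

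| Assumed correlation between tests | k = 3 | k = 4 | k = 5 |
|---|---|---|---|
| 0.3 | 13.6% | 17.3% | 20.9% |
| 0.5 | 12.5% | 15.7% | 18.3% |
| 0.7 | 10.9% | 13.0% | 14.8% |

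These rates describe the PSFS conclusion only if one positive test out of k is taken as success. Each single test keeps its own 5% level.

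**Reading B: all activity scores stacked as separate records, with the person ignored.** For m activities per person and within-person correlation ρ of the analysed changes, the variance is understated by the design effect 1 + (m − 1)ρ. The true level of a nominal 5% test is 2 × [1 − Φ(1.96 / √(design effect))]. For m = 3 and ρ = 0.5, the design effect is 2.0, 1.96 / 1.414 = 1.386, and the level is 16.6%.

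| Assumed ρ | Design effect, m = 3 / 4 / 5 | True level, m = 3 / 4 / 5 |
|---|---|---|
| 0.3 | 1.6 / 1.9 / 2.2 | 12.1% / 15.5% / 18.6% |
| 0.5 | 2.0 / 2.5 / 3.0 | 16.6% / 21.5% / 25.8% |
| 0.7 | 2.4 / 3.1 / 3.8 | 20.6% / 26.6% / 31.5% |

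**Reading C: a mixed model with activities nested in participants.** This gives one treatment contrast, allows for the correlation and needs no total. It has neither problem.

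The article names linear mixed models as one of two general options for all outcomes. It does not tie them to the several PSFS scores per person, so it does not choose between A, B and C.

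**The case against.** A reader might infer that the PSFS analysis must be either multiple tests or pseudo-replication, and so has the wrong error rate in any case. The article does not support that. Reading C is open under the methods it names, and analysing one pre-specified activity would also avoid both problems.

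Nor does the scoring sentence say that scores from one person will be treated as statistically independent. It sits in the description of the instrument, next to the statement about the total, and may mean only that items are not summed. Reading B is therefore a possibility and not a stated plan.

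A reader might also infer that tests on activities 4 and 5 are biased between arms because participants select themselves into them. Under Randomisation and allocation concealment, envelopes are opened only once baseline assessment is complete, and the PSFS is a baseline measure. If activities are named then, those who name four or five form a subgroup defined before randomisation. The comparison stays randomised; the cost is fewer participants and a different target population.

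The FIHOA could be added to the count, giving 4 to 6 tests and 18.5% to 26.5% if independent. That mixes in a separate question. Two unadjusted primary instruments give 1 − 0.95² = 9.75% if independent, even with a perfectly defined PSFS score.

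Finally, this is a condensed article, and the model for repeated items could be left to an analysis plan. That would answer mere silence. Here the article states a rule, and a plan that defined a participant-level score would have to depart from it. These objections narrow the point but do not remove it.

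**Conclusion.** The point holds in this form: the PSFS is primary, its stated scoring rule excludes a participant-level score, and no single treatment contrast is named in its place.

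On the most literal reading, the chance of at least one false-positive PSFS test is 14.3% to 22.6%, assuming independent tests and success on any one of them. It falls to 10.9% to 14.8% at an assumed correlation of 0.7. Stacking would put a nominal 5% test at about 12-19%, 17-26% or 21-32% for assumed ρ of 0.3, 0.5 or 0.7, with the same number of activities for everyone. All correlations are assumptions, because the article gives none.

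The FIHOA analysis and the sample size stand. How FIHOA and PSFS jointly determine success is a separate matter that this point does not settle.

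**What to change.** Replace the scoring sentence with wording such as: *The PSFS score is the participant's mean over the activities nominated at baseline. The same activities are re-scored at 3 and 6 months, and one score per participant and time point is analysed. Scores for single activities are reported descriptively only.*

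An alternative that serves the same purpose is one treatment contrast from a linear mixed model on the activity scores with a participant random effect, named in the text as the PSFS primary analysis. The two can weight participants slightly differently when they name different numbers of activities, so one should be chosen in advance.

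The cost is one sentence and one derived variable or model statement, with no new data and no change in sample size. The downside is that averaging hides differences between activities; the descriptive item-level report keeps these visible.
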